### **Training protocol**

One reason why the results of previous studies were not convincing enough was that the PFMT program was not properly designed or the intensity of the PFMT regime was not sufficient. According to the 2019 NICE guideline on the management of UI and POP in women, PFMT programmes should comprise at least 8 contractions performed 3 times per day. An intensive training protocol was proposed by some studies, consisting of three sets of ten contractions at maximum intensity holding for 6 seconds each, three or four times a week.

Both study groups will be instructed to follow the same training protocol during the first three months after randomization. The protocol includes the performance of three sets of fast and slow contractions completed per day in the supine position. Each set lasts for 6 min and comprises three replicates. Each replicate consists of 8 maximal contractions (held for 6 seconds with a 6-second rest) followed by 4 fast contractions (held for 1 second with a 1-second rest) and a 30-second rest between each replicate.

### **Study device**

The study device adopted in our study was designed and developed by the principal investigators of this study and Shenzhen XFT Medical Limited in September 2021 for scientific

research use only. The wearable PFMT study device named XFT-0010CK is a digital device with an intravaginal insert and a battery pack. The device has a screen that is able to show the real-time value of the vaginal resting pressure and voluntary contraction pressure in units of mmHg. The intravaginal insert is a vaginal air-filled probe with the gas filled automatically when it starts to work. The two parts are combined with a thin air tube. The whole device is connected to the PFMT study app by Bluetooth to record the progress of and compliance with PFMT. There are two modes of the device: assessment and training modes. In regard to the assessment mode, the device is able to assess the PFM strength by the patients themselves following the instructions. The training mode is the significant mode to guide patients to complete PFMT by following the training protocol and visualizing the real-time progress of PFM contraction via the PFMT study app. The biofeedback is provided according to the pressure collected by the vaginal air-filled probe during training.

## **APP**

Patients in both groups will be instructed to download and install an app named the PFMT study app from the App Store, which is available for both Android and iOS smartphones and was developed by our research group in collaboration with software engineers based on the study protocol to guide both groups through the study as shown in Fig 1. In both groups, patients can complete the questionnaires via the app and receive a reminder within 1 week before the indicated time. Additionally, the app will send daily push reminders to both groups to remind them to complete daily PFMT. Both groups can upload the exercise diaries via the app. The app will also provide a different operation interface and function according to the

allocation status. The study device connects to the PFMT study app using Bluetooth. In the intervention group, the app can support the performance of the PFM contraction by providing visual biofeedback on the PFM contraction over time while storing the duration of, frequency of and compliance with training. The control group will use the same training video three times a day.

## **Outcome measures**

### **Primary outcome measure**

The primary outcome will be evaluated by the International Consultation on Incontinence Questionnaire-Urinary Incontinence short form (ICIQ-UI SF), a patient-reported outcome measure (PROM) for the severity of UI. The questionnaire will be administered in the Chinese and the Chinese version has been validated. It contains 4 items including urine leakage (score of 0 = never to 5 = always), amount of urine leakage (scores of 0, 2, 4, 6 for increasing amounts per episode), and impact of the urine leakage on life (score of 0 = not at all to 10 = a great deal) and types of leakage symptoms experienced in the previous 4 weeks. The ICIQ-UI SF score is the sum of the first three items ranging from 0 to 21 divided into mild (0–5), moderate (5–13) and severe (13–21). Higher scores reflect greater severity.

### **Secondary outcome measures**

#### *PFM strength*

The PFM strength will be evaluated by subjective (vaginal palpation) and objective (manometer) measurements. During the assessments, each participant will be examined in the lithotomy position with an empty bladder and the head of the bed inclined at a 30° angle. The subjective

PFM strength will be measured by digital vaginal palpation based on the modified Oxford grading scale (MOS). Patients will be asked to perform a maximum contraction of the muscles to squeeze and lift against the resistance provided by the assessors' fingers in the vagina. The subjective PFM strength will be classified within the range of Grades 0-5, with higher grades reflecting better strength (0 (no contraction), 1 (flicker contraction), 2 (weak contraction), 3 (moderate contraction), 4 (good contraction), 5 (strong contraction)).

The objective PFM strength will be defined as the maximum voluntary contraction pressure (MVCP), which is referred to as the force-generating capacity of a muscle and evaluated through an intra-vaginal manometer (a vaginal balloon probe filled with 20 ml gas) connected to a PHENIX USB 8 neuromuscular stimulation therapy system, which is equal to a high-precision pressure transducer (Electronic Concept Lignon Innovation, Montpellier, France). MVCP will be calculated as the difference between the vaginal resting pressure (VRP) and its peak pressure during a maximum voluntary contraction. The patients will be asked to perform maximum contractions of the PFMs three times without using the abdominal, gluteal, or hip adductor muscles during the contractions. Each contraction will have an interval of 15 seconds. The outcome will be recorded as the average of three measurements. Higher pressure is related to greater strength.

#### *Quality of life*

Quality of life will be evaluated by the Chinese version of Incontinence Quality of Life Instrument (I-QOL) with 22 items. Its Chinese version has not been validated. The instrument has 3 subscales: (1) avoidance and limiting behaviour, (2) psychosocial impacts, and (3) social

embarrassment. All items are evaluated using a 5-point Likert-type scale. The scores will be summed and transformed to a 0 to 100 scale. Higher scores represent better quality of life.

#### *Broome pelvic muscle self-efficacy scale (BPMSES)*

The questionnaire employed in our study to evaluate the outcomes of self-efficacy is reliable and validated. We will use a Chinese version with a 23-item rating scale consisting of two domains: efficacy expectations and outcome expectations. In the efficacy expectations domain, participants will demonstrate how confident they are in performing PFMT. In the outcome expectations domain, participants will indicate their level of confidence that the training will prevent unwanted urine leakage. The score ranges from 0 to 100. The higher the score is, the greater the self-efficacy perceived by the participant.

#### *Curing and improvement in SUI*

Cure in SUI was defined as the total score on the ICIQ-UI SF=0 at the endpoint of 3 months of treatment. Improvement in SUI was defined as a reduction in the ICIQ-UI SF score of  $\geq 3$  points compared with the endpoint of 3 months of treatment at baseline.

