## 15 Patient selection and recruitment

16 Since March 2022, women who present for regular postpartum clinic visits at the 5 participating  
17 tertiary hospitals and report new-onset SUI or SUI-predominant MUI within three months after  
18 delivery will be instructed on the project. Afterwards, the well-trained physicians in each  
19 participating centre will screen the potentially eligible patients. Patients who meet all the  
20 criteria and express an interest in participating will be recruited. After participant eligibility is  
21 confirmed and consent obtained, the site physicians will complete the randomization by

entering the patient's name, date of birth, phone number and picture of the consent form into the computer-generated randomization program in real time. The allocation status will not be concealed from nonblinded physicians who will perform the recruitment, supervision and follow-up or from the patients but will be concealed from the assessment physicians. The inclusion and exclusion criteria are as follows:

Inclusion Criteria: 1) 6 weeks < after delivery < 3 months postpartum; 2) Clinically diagnosed SUI as the primary problem. We will consider SUI and MUI following the definition recognized by international guidelines; 3) Women aged 18 years or older

Exclusion Criteria: 1) Urgency UI alone; 2) Pelvic Organ Prolapse Quantification (POP-Q) stage  $\geq 2$ ; 3) Third- and fourth-degree perineal tears; 4) Presence of diastasis recti abdominis and chronic pelvic pain as the primary problem needing treatment; 5) A history of SUI before pregnancy; 6) Previous pelvic surgery; 7) Malignant pelvic cancer; 8) Urogenital infections; 9) Receipt of formal instruction on PFMT in the past 5 years; 10) Unsuitability to participate because of significant diseases; 11) Others: Inability to contract the PFMs on digital examination when requested; inability to use the device in the vagina.

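### Cure and improvement carry no baseline condition, so a woman scoring 0 at both visits counts as cured and one starting at 0 to 2 can never count as improved

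*Protocol*

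**What the plan says.** Curing and improvement in SUI fixes two responder outcomes. The first is "Cure in SUI was defined as the total score on the ICIQ-UI SF=0 at the endpoint of 3 months of treatment", with no reference to the baseline score. The second is "Improvement in SUI was defined as a reduction in the ICIQ-UI SF score of" at least 3 points between baseline and 3 months (the sentence garbles the order of the two time points, but the intent is clear).

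Patient selection and recruitment approaches women who "report new-onset SUI or SUI-predominant MUI within three months after" delivery and requires "Clinically diagnosed SUI as the primary problem". No inclusion or exclusion criterion refers to an ICIQ-UI SF score.

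Primary outcome measure describes the score as a sum of three items: how often urine leaks (0 to 5), how much leaks (0 to 6 in steps of 2) and how far leakage affects daily life (0 to 10). The total runs from 0 to 21, and the mild band starts at 0. A recall period is given with the fourth, unscored item: "types of leakage symptoms experienced in the previous 4 weeks".

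**The concern.** Entry is by diagnosis and report, while response is by score, and nothing ties the two together. Women enter between 6 weeks and 3 months after delivery and may report leakage from any time since delivery, but the recall period that the protocol gives is 4 weeks. A woman whose leakage has recently stopped is not excluded by any score and could have a baseline total of 0.

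If she stays at 0, she meets the definition of cure although her score had no room to change. She cannot meet the definition of improvement, and neither can a woman starting at 1 or 2. The first case adds to the cure count in both arms. The second leaves in the improvement denominator women for whom the event is impossible. At stake are the reported percentages for two secondary outcomes and some of the contrast between arms.

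**Working it through.** **1. The plan's own figure.** The protocol gives no figure for cure or improvement. Its only calculation is for the primary score (Statistical analysis): difference 2.5, SD 8.1, two-sided 0.05, power 0.90.

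- Normal approximation: n = 2 × (1.960 + 1.282)² × (8.1/2.5)² ≈ 2 × 10.507 × 10.498 = 220.6, so 221 per group.
- Two-sample t-test version: 221.57, so 222 per group, as stated.
- Allowing 10% loss: 222/0.90 = 246.7, so 247; the plan recruits 250.

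The responder definitions do not enter this, so the sample size reproduces and is untouched.

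**2. What each baseline total allows.** Items score 0 to 5; 0, 2, 4 or 6; and 0 to 10. Every total from 0 to 21 is therefore possible. Improvement needs a 3-month total no higher than baseline minus 3.

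| Baseline total | Counts as cure at 3 months | Counts as improvement at 3 months |
|---|---|---|
| 0 | 0 (no change) | never |
| 1 or 2 | 0 | never |
| 3 | 0 | 0 only |
| 4 | 0 | 0 or 1 |
| 5 | 0 | 0, 1 or 2 |
| 6 | 0 | 0 to 3 |

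Two anomalies follow: a cure without any change at baseline 0, and a cure that is not an improvement at baseline 1 or 2.

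**3. Effect on cure.** Let f be the share of each arm at 0 at baseline who remain at 0, and p the true cure rate among the others. Observed cure = f + (1 − f)p, and the difference between arms is multiplied by (1 − f). Assume p = 30% v 20%:

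- f = 5%: 5 + 0.95 × 30 = 33.5% v 5 + 0.95 × 20 = 24.0%. The difference is 9.5 points instead of 10, and the ratio 1.40 instead of 1.50.
- f = 10%: 10 + 0.90 × 30 = 37% v 10 + 0.90 × 20 = 28%. The difference is 9.0 points and the ratio 1.32.

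**4. Effect on improvement.** Let f now be the share with baseline 0 to 2, and q the true improvement rate among the others. Observed improvement = (1 − f)q. Assume q = 63% v 50% and f = 5%: 0.95 × 63 = 59.85% v 0.95 × 50 = 47.5%. The difference is 12.35 points instead of 13. The ratio stays at 63/50 = 59.85/47.5 = 1.26, so only the percentages, the difference and the power are affected.

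**5. Effect on power.** Normal approximation for two proportions, 222 per arm, two-sided 0.05, with all rates assumed:

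| f | Cure, true 25% v 15% | Improvement, true 63% v 50% |
|---|---|---|
| 0 | 75% | 79% |
| 2% | 71% | 77% |
| 5% | 65% | 74% |
| 10% | 56% | 70% |

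Neither f nor the true rates appear in the protocol, so these are ranges and not estimates.

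**The case against.** The strongest reply is that the case is rare. Trained physicians screen, and stress incontinence must be the primary problem, so a woman who no longer leaks would seldom be enrolled. This stands: the case is possible but should be uncommon, and the protocol offers no baseline distribution to say more.

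A second reply is that denominators may be set in a statistical analysis plan that is not at hand. That is fair for denominators, but the protocol itself fixes the definition of cure, and it does so without a baseline condition.

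A reader might also infer more than the documents support:

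- *That improvement and cure are the same event for every woman with mild leakage.* If answers are coherent, a leaking woman scores at least 1 + 2 + 0 = 3, and then any fall of 3 points from 3, 4 or 5 does mean 0. The protocol states no such constraint. Its plain sum allows totals of 1 or 2, for example some impact without leakage. Strictly, the two coincide only at baseline 3.
- *That this overlap distorts the outcomes.* A fall from 3, 4 or 5 to 0 is a real cure and a real improvement. The protocol does not present improvement as partial response, and overlapping endpoints are not an error.
- *That recovery before entry would be credited to the treatment.* Allocation is randomized 1:1 and the responder outcomes are compared between groups. Such recovery is expected equally in both arms and creates no treatment effect.

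**Conclusion.** The definitions need a baseline condition. As written, a woman at 0 at both visits is a cure, and women starting at 0 to 2 can never improve. The consequence is inflated cure percentages, deflated improvement percentages and a modest shrinking of the between-arm differences, not bias toward one arm. In the illustration the cure difference falls from 10 to 9.5 points if 5% of each arm are at 0 throughout, and to 9.0 points if 10% are. This rests on assumed rates, on equal shares in both arms, and on those women remaining at 0. The concern is confined to two secondary outcomes; the primary outcome and its sample size stand.

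**What to change.** Reword the two definitions in Curing and improvement in SUI:

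- Cure: baseline score above 0 and score of 0 at 3 months, with women whose baseline is above 0 as the denominator.
- Improvement: a fall of at least 3 points from baseline to 3 months, among women with a baseline of at least 3. This also repairs the garbled time order.
- State that cured women whose score fell by at least 3 points also count as improved.
- Keep the version with all randomized women in the denominator as a sensitivity analysis for both outcomes.

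No new data are needed. Randomization and masking places the baseline assessment before allocation, so the restriction uses a pre-randomization variable and keeps the arms comparable. One point should be confirmed: Data collection has the questionnaire completed in the study app, whereas Intervention describes supervised download of the app after randomization. The text should make clear that the baseline score is recorded before allocation.

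The cost is that a few randomized women leave these two secondary denominators, and the cure percentage may look slightly lower. Eligibility need not change. Recruitment has run since March 2022, and adding a score threshold now would mix two entry populations.

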#### *Patient adherence to treatment*

There is no universally accepted standard for adherence. In our study, patients' adherence to treatment will be determined as the frequency of exercises anticipated for 3 months of supervised treatment, which will be subjectively self-reported and objectively device-recorded. Patients' overall adherence will be categorized as follows:  $50\% \leq$  low adherence;  $50\% - 75\%$  = medium adherence; and  $\geq 75\%$  = high adherence.

#### **Statistical analysis**

The primary outcome of this study is the ICIQ-UI SF score. An ICIQ-UI SF minimal clinically important difference of 2.5 points was reported by Nyström E in 2015. We referred to two RCT studies reporting ICIQ-UI SF data as the primary outcome for women with SUI with 5-month and 6-month follow-up indicated an assumed standard deviation (SD) of 5. Another study determined a SD of 10 because they expected that the SD at the 24-month time point could possibly be as high as 10. According to our study design, it would be reasonable for us to expect a SD of 8.1 at the 12-month time point. On this basis, the sample-size calculation in our study is expected to be based on a significant difference of 2.5 points in ICIQ-UI SF scores (SD of 8.1) as the primary outcome between the groups. A sample size of 222 participants per group will detect this difference calculated through PASS 15, with a power of 0.9 and a two-sided significance level of 0.05. Thus, a total of 500 women will be recruited (250 women per group), allowing for approximately 10% loss to follow-up during the 12-month period.

The data will be analysed by SPSS version 26.0 (IBM, Armonk, New York, USA). Continuous variables conforming to a normal distribution are presented as the means  $\pm$  standard deviations (SDs), within-group comparisons will be analyzed with paired-samples t tests, and two independent samples t tests will be used for between-group comparisons. If the data is nonnormally distributed and presented as medians and interquartile ranges, the Wilcoxon signed rank test will be used for analyses within the groups, and the Mann-Whitney U test will be used for comparisons between two groups. Categorical variables are presented as n (%), the chi-square test will be used for within-group comparisons, and Fisher's precision probability test will be used for between-group comparisons. The relationship between self-reported

211 adherence and device-reported adherence will be assessed using a scatter plot.  $P < 0.05$  will be  
212 considered significant.

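### The primary comparison is left to an undefined normality judgement, and its rank branch does not estimate the 2.5-point mean difference on which the trial is sized

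*Protocol*

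**What the plan says.** All references are to the protocol.

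- **Outcome.** Statistical analysis: "The primary outcome of this study is the ICIQ-UI SF score". Under Primary outcome measure it is the "sum of the first three items ranging from 0 to 21".
- **Planning.** Statistical analysis bases the sample size on a "significant difference of 2.5 points in ICIQ-UI SF scores (SD of 8.1) as the primary outcome between the groups", with 90% power and two-sided 5% significance, giving 222 per group and 250 recruited per group.
- **Test.** The same section gives one rule for continuous variables. Normal data are shown as means and SDs and compared between groups by the two-sample t test. "If the data is nonnormally distributed and presented as medians and interquartile ranges", "the Mann-Whitney U test will be used for comparisons between two groups".
- **Floor.** Curing and improvement in SUI: "Cure in SUI was defined as the total score on the ICIQ-UI SF=0" at 3 months.

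The primary outcome is not exempted from the rule. The section names no normality test or threshold. It does not say whether the 3-month score or the change from baseline is examined, or whether this is done by group or pooled.

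**The concern.** The sample size is a calculation about means. The rule for the test lets the observed data move the primary comparison off that scale. Two things are at stake.

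1. **Pre-specification.** Two analysts who follow the protocol faithfully could reach different primary tests, depending on how each checks normality.
2. **The effect estimate.** Mann-Whitney compares ranks, and the protocol pairs it with medians and interquartile ranges. Nothing in that branch gives a between-group mean difference with a confidence interval, which a reader needs to judge the result against the 2.5 points used in planning.

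The shape of the score makes the rank branch a realistic prospect: it is bounded, takes whole numbers, and places every cured woman at exactly 0.

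**Working it through.** **1. The plan's own figure.** Inputs from Statistical analysis: difference 2.5, SD 8.1, power 0.90, two-sided alpha 0.05.

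n per group = 2 × (1.960 + 1.282)² × (8.1/2.5)² ≈ 2 × 10.51 × 10.50 ≈ 220.6, so 221 by the normal approximation. The noncentral-t calculation gives 222, with power 0.9006. The stated 222 is reproduced as a two-sample comparison of means. Allowing 10% loss, 222/0.90 = 246.7, so 247, against 250 planned.

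**2. Would a normality check reject?** The protocol gives no expected cure rate, so the share of zeros is an assumption and is varied. The other scores are rounded normal values within 1-21, SD 4, centre 7 or 9, with n = 222 and tests at 5%. Percentage of samples of the 3-month score in which normality was rejected:

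| Zeros | Shapiro-Wilk | Lilliefors |
|---|---|---|
| 5% | 93-100% | 93-98% |
| 10% | 100% | 94-99% |
| 20-40% | 100% | 100% |

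**3. The planning SD points the same way.** A uniform distribution over the scale has SD 21/√12 = 6.1 (continuous) or √((22² − 1)/12) = 6.3 (whole numbers). The planned 8.1 is wider than either. A normal distribution with SD 8.1 would put 29% of its mass outside 0-21 at mean 5, 22% at mean 8 and 19% at mean 10.5. The planning assumption therefore cannot describe normal data on this scale.

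**4. Where the answer changes.** The result in step 2 depends on which variable is checked and how. With a centre of 7 and SD 4, Shapiro-Wilk rejected the change score in only about 40-70% of samples. Skewness of the 3-month score was modest (0.15-0.61 for 5-40% zeros at centre 7), so a check that tolerates moderate skewness would keep the t test. The protocol permits any of these checks.

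**5. Can medians stand in for the mean difference?** Not in general. Suppose, for illustration only, that 55% of women in each group score 0. Both medians are then 0 whatever happens to the other 45%. A mean difference of 2.5 would need those remaining women to differ by 2.5/0.45 = 5.6 points on average, and the median difference would still be 0. A simulated case of this kind gave a mean difference of 2.54 and a median difference of 0.

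**6. Error rate.** With identical groups (20% zeros, 222 per group), rejection at 5% was 0.049 for the t test, 0.048 for Mann-Whitney and 0.048 for the rule that switches on Shapiro-Wilk. The switch does not inflate type I error here. The t test also needs no switch to hold its level with such data.

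**The case against.** **A switch is not certain.** A reader might infer that the primary test will almost surely become Mann-Whitney. The documents do not support that. They name no normality test and give no cure rate. The improvement endpoint is defined by change from baseline, so a change-score analysis is conceivable, and there the check is far from one-sided. This objection stands. It limits the claim about likelihood, but it also shows that the rule does not determine the analysis.

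**No false-positive harm.** A reader might also infer that choosing the test from the data inflates type I error. The simulation does not show this, and power was similar in most scenarios tried. This stands too.

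**Blinding.** Randomization and masking says that those who analyse the data are blinded to allocation. That limits any steering of the choice towards a favoured group. It does not settle which quantity is estimated.

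**A rank test can answer the question.** The Introduction asks whether adding biofeedback is superior, and a rank test can address superiority. A Hodges-Lehmann shift in points, with an interval, can also accompany Mann-Whitney. Both are true. But the protocol plans no such estimate, and it would not be the mean difference used to size the trial.

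**Baseline adjustment.** It would be wrong to blame its absence on the switch, because the planned t test does not adjust either.

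**An analysis plan may settle it.** One may exist and is not shown. The point concerns a rule that the protocol does write down: a plan that followed it would inherit the problem, and one that fixed a single analysis would depart from it.

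**Conclusion.** The point holds as a defect of pre-specification and of the effect estimate, not of error control. The trial is sized on a mean difference (222 per group, reproduced), while the test rule lets an unstated criterion replace the mean comparison with ranks and medians.

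Under a formal test of the 3-month score the replacement is very likely: about 93-100% of samples with 5% or more zeros. That figure rests on an assumed centre of 7 or 9, SD 4 and share of zeros, none of which the protocol gives. Under a change score or a lenient skewness rule the t test could be kept. Type I error is about 5% either way. The example with medians at 0 shows only that medians and means can part; it does not predict that they will in this trial.

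The correction is worth making because it is cheap and removes the ambiguity.

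**What to change.** In Statistical analysis, remove the normality switch for the primary outcome and state one primary analysis that applies whatever the distribution: the between-group mean difference in the 3-month ICIQ-UI SF score with its 95% confidence interval, from a model adjusted for baseline score and study centre, with robust or bootstrap standard errors. Both covariates are already listed under Data collection. Fixing the comparison is the essential part; the adjustment is an added improvement. Name Mann-Whitney as a sensitivity analysis, and report means and SDs beside medians and interquartile ranges.

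Cost: wording only, with no new data. The planned 222 per group is unchanged, since it was derived for a comparison of means. The possible downside is slightly less power than a rank test if scores prove very skewed.

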#### **Data collection**

The demographics and health information of the patients will be collected by the self-designed electronic questionnaire via the PFMT study app at baseline and will include age, height, weight, study centre, weight gain during pregnancy, menstruation, feeding patterns, occupation type and position, educational level, toileting position, smoking, family history, sexual activity, labour and physical activity and medical history. Obstetrical data, including the delivery date, gravidity and parity, delivery mode, newborn weight, will be collected from the electronic medical records. Both groups will be assessed by repeated questionnaires, physical examination and manometry at baseline (pretest) and 3 months (at the end-point of intervention). The validated questionnaires used to evaluate the outcomes will be completed by the patients via the PFMT study app each time before the assessment is performed. Physical examination and manometry will be performed by the same assessment physician at each participating centre who is blinded to the allocation status. The patients' adherence to and compliance with treatment will be subjectively recorded by a self-reported training diary via the PFMT study app and objectively recorded by the biofeedback device in the intervention group. In the control group, the adherence and compliance will be simply recorded by a self-reported training diary via the PFMT study app.

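### Chi-square is specified for baseline-to-3-month comparisons of categorical variables, which are paired observations and need a paired test

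*Protocol*

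**What the plan says.** The Statistical analysis section of the protocol assigns a test to each type of data, once for comparisons within a group and once for comparisons between groups.

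- Normally distributed continuous data: "within-group comparisons will be analyzed with paired-samples t tests".
- Non-normal data: "the Wilcoxon signed rank test will be used for analyses within the groups".
- Categorical data: "the chi-square test will be used for within-group comparisons", while "Fisher's precision probability test will be used for between-group comparisons".

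The Data collection section gives the timing: "Both groups will be assessed by repeated questionnaires, physical examination and manometry at baseline (pretest) and 3 months (at the end-point of intervention". Two categorical measures can therefore exist at both visits. One is the palpation grade on the modified Oxford scale (PFM strength section): "The subjective PFM strength will be classified within the range of Grades 0-5". The other is the ICIQ-UI SF severity class (Primary outcome measure section), where the score is "divided into mild (0–5), moderate (5–13) and severe (13–21".

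The section closes by setting one significance threshold, P below 0.05, for its tests. It does not exempt the within-group ones.

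**The concern.** The protocol itself fixes the meaning of a within-group comparison. Paired t and Wilcoxon signed-rank tests make sense only for two measurements on the same woman. The categorical clause must mean the same comparison, yet it names a test for independent samples. The plan is right for two data types and wrong for the third.

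At stake is whether the P values for before-after change in a categorical measure mean what they say. Judged at 0.05, an unpaired test on positively correlated visits will tend to miss change that a paired test would detect. The clause also leaves the layout of the table open. In one layout the test is badly calibrated; in the other it answers a different question.

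**Working it through.** **The plan's own figure first.** The only calculation in the protocol is for the primary outcome: difference 2.5, SD 8.1, "with a power of 0.9 and a two-sided significance level of 0.05". The normal formula gives n = 2 × (1.960 + 1.282)² × 8.1² / 2.5² ≈ 220.6, so 221 per group. The t-based solution is 221.57, so 222, as stated. Allowing for 10% loss, 222 / 0.9 = 246.7, so 247, which the plan rounds up to 250. The sample size reproduces and does not depend on this point.

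**Inputs for the check.** From the protocol: 222 evaluable women in a group, two-sided alpha 0.05, the same women at two visits. Assumed, because the protocol gives no figures: a binary variable with a true proportion of 0.5 at baseline, and a within-woman correlation phi from 0.2 to 0.7. To help place phi: if a binary variable is an underlying normal scale cut at its median, a latent correlation of 0.5 gives phi = (2/π) × arcsin(0.5) = 0.33.

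**Layout 1: the two visits entered as if they were two separate samples.**

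With no true change, the variance of the difference in proportions is (1 − phi) times the variance chi-square assumes. The true error rate is therefore

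2 × [1 − Φ(1.96 / √(1 − phi))].

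At phi = 0.5: 1.96 / √0.5 = 2.77, so the error rate is 0.0056.

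For power, take a true fall from 0.5 to 0.4.

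- Standard error used by chi-square: √(2 × 0.45 × 0.55 / 222) = 0.0472.
- True standard error at phi = 0.5: √((0.25 + 0.24 − 2 × 0.5 × 0.245) / 222) = 0.0332.
- Power of chi-square: Φ((0.10 − 1.96 × 0.0472) / 0.0332) = Φ(0.22) ≈ 0.59.
- McNemar uses the discordant fraction. The fraction positive at both visits is 0.5 × 0.4 + 0.5 × 0.245 = 0.322, so the discordant fraction is 0.9 − 2 × 0.322 ≈ 0.255. Its null standard error is √(0.255 / 222) = 0.0339, and power is Φ((0.10 − 1.96 × 0.0339) / 0.0332) = Φ(1.01) ≈ 0.84. Simulation gives 0.85.

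Results over the range (simulation with 200,000 runs per row):

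| phi | Chi-square error, formula | Chi-square error, simulated | McNemar error, simulated | Chi-square power | McNemar power |
|---|---|---|---|---|---|
| 0.2 | 2.8% | 2.9% | 5.0% | 57% | 66% |
| 0.3 | 1.9% | 2.0% | 5.1% | 58% | 72% |
| 0.5 | 0.6% | 0.6% | 5.0% | 59% | 85% |
| 0.7 | 0.03% | 0.05% | 5.1% | 61% | 98% |

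The test is correctly calibrated only at phi = 0. It would be too liberal under negative correlation (7.4% at phi = −0.2 by the formula).

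**One worked table.** Of 222 women, 91 are positive at both visits, 71 negative at both, 20 positive only at baseline and 40 positive only at 3 months. The margins are 111 and 131 positive.

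- Chi-square on the margins: 3.63, P = 0.057.
- McNemar: (20 − 40)² / (20 + 40) = 6.67, P = 0.010 (exact 0.013).

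The two tests fall on opposite sides of the protocol's threshold.

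**Layout 2: the baseline-by-3-month cross-table.** Here chi-square asks whether the visits are associated. With no change at all in the proportion, it rejects in 85% of simulated runs at phi = 0.2 and in about 100% at phi = 0.5. Those rejections say nothing about change.

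**The case against.** Five things can be said on the other side.

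*The authors may have meant McNemar's chi-square.* Possible, but the text does not support it. The paragraph names its other two paired tests explicitly and gives no paired version here. If that was the intent, the sentence still needs to say so. Because this is a stated choice, a separate analysis plan that may exist does not excuse it.

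*The figures describe an endpoint the protocol does not name.* This stands. Cure, improvement and adherence category are defined only at or over 3 months, so they have no before-after version. The named measures available twice are ordered with several levels, and the protocol does not say that the severity class will be tested. The table above illustrates the mechanism. It is not an estimate for the Oxford grade or the severity class, and the loss for those has not been calculated.

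*The size depends on phi.* This also stands. At phi = 0.2 the loss of power is modest (57% against 66%).

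*The Oxford grade may not be treated as categorical.* This stands too. A reader might infer that the plan analyses the grade with unordered chi-square and Fisher tests and so ignores its ordering. The protocol does not say which branch the grade follows. Under the non-normal branch it would already receive rank-based tests.

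*Within-group tests do not carry the treatment comparison.* True, and it limits the consequence. But the protocol does not label these tests descriptive. Whether it should, or should use a modelled ordinal comparison between groups, is a matter of preference and not part of this point.

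**Conclusion.** The clause is wrong as written: it names a test for independent samples for a comparison that the same paragraph treats as paired for every other data type. That conclusion rests on the text alone and needs no assumption.

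The size does rest on assumptions. For a hypothetical binary variable near 50% in 222 women, with the visits treated as separate samples and phi between 0.2 and 0.7, the true error rate is 2.8% down to 0.03%, and power for a 10-point change is about 57–61% against 66–98% for McNemar.

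Two stronger readings are not supported. A reader might infer that the error inflates false positives; in the first layout with positive correlation it does the opposite and hides real change. A reader might also infer that the trial's answer on the device is compromised. It is not: the trial is powered on a between-group difference in ICIQ-UI SF score, and Fisher's test is valid for two independent arms. Only secondary within-group P values for categorical variables are affected. The correction is worth making, but the scope is narrow.

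**What to change.** In the Statistical analysis section, replace the chi-square test for within-group categorical comparisons with:

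- McNemar's test for any binary variable measured at both visits (exact form if discordant pairs are few);
- the Wilcoxon signed-rank test, or Stuart-Maxwell, for ordered or multi-category variables such as the Oxford grade or the severity class, if these are analysed as categorical.

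The cost is one sentence. No new data, visits or participants are needed, the sample size is unchanged, and the Wilcoxon signed-rank test is already in the plan for non-normal data.
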